# **3. Trial Interventions**

## **3.1 Interventions**

The trial will assess the impact of the InterFACE-AR system on two interventions designed to provide decision support during pediatric in-hospital cardiac arrest:

- **Intervention A: *InterFACE-AR System*** – data collected from the Guiding-Pad app will be fed to the two AR headsets for the team leader and medication nurse to provide role-specific decision support, and to the TeamScreen, which will be mounted on a wall, in clear view for the entire resuscitation team to see.
- **Control group: *AHA PALS Pocket Reference Cards*** – all participants will have access to the AHA PALS pocket reference cards, which is the mostly commonly used cognitive aid during resuscitation.

### 3.2 Orientation and Simulation Scenarios

Following randomization (1:1 ratio), all participants will view a standardized orientation video describing the clinical environment, equipment, manikin functionality, and participant roles. The intervention group will receive additional orientation to the InterFACE-AR system, comprised of (1) a 10-minute instructional video describing the system's components and functions; (2) a 5-minute hands-on training session using the assigned device (Guiding Pad app for medication nurse, AR headsets for team leader and medication nurse) and comprised of opportunity to use and practice their assigned task, guided by a checklist, and (3) a 4-minute verbal scripted walk-through scenario allowing participants to use the system in their assigned roles.

A 12-minute CA simulation scenario (pulseless electrical activity [4 minutes] → pulseless ventricular tachycardia [4 minutes] → ventricular fibrillation [4 minutes] → return of spontaneous circulation) will be run by both groups. Both recruitment sites will utilize the identical pediatric manikin (SimJunior™, Laerdal Corporation), specifically designed and calibrated for CPR training. All simulation scenarios will be tightly standardized by using a scenario template with highly scripted actor roles and patient progression. After the session, participants will be instructed not to disclose any information from the scenario to other participants to prevent any preparation bias.

## 4. Outcomes

**The Primary outcome measure** will be the time to first dose of epinephrine, defined as the interval in seconds from recognition of CA at the start of the scenario to completion of epinephrine injection.

**Secondary outcome measures will be:**

- Adherence to ALS guidelines: (i) Time to initiation of CPR; (ii) Time to defibrillation; (iii) Time to delivery of first and second drug to treat underlying condition; (iv) Time to secure definitive airway; (v) Medication errors (absolute count and frequency; assessed immediately post-scenario by measuring residual volumes in collected and labeled syringes), as described previously in one of our RCTs as a deviation in drug dose exceeding 10% from the correct weight-based dose according to

predefined, expert consensus-based criteria (vi) Frequency and duration for pauses in CPR (captured by video review, see below).

- CPR quality: (i) Chest compression fraction (CCF) (percentage of time performing CC during cardiac arrest); and (ii) Peri-shock pause durations.
- User experience: assessed using the User Experience Questionnaire (UEQ), a 26-item, 7-point scale questionnaire with supportive validity evidence, grouped into 6 scales covering efficiency, perspicuity dependability, attractiveness, stimulation, and novelty.
- Technology acceptance: measured with the Technology Acceptance Model (TAM) survey, evaluating perceived usefulness and ease of use.

## 5. Participant Timeline

The total study period to enrol all participants will take 1 month.

| TIMEPOINT                                     | STUDY PERIOD  |           |                                 |                 |           |
|-----------------------------------------------|---------------|-----------|---------------------------------|-----------------|-----------|
|                                               | Pre-enrolment | Enrolment | Pre-study baseline / allocation | 12-min scenario | Close-out |
|                                               | $-t_2$        | $-t_1$    | $t_0$                           | $t_1$           | $t_x$     |
| STUDY PROCEDURES                              |               |           |                                 |                 |           |
| Invitation to participate                     | ✓             |           |                                 |                 |           |
| Recruitment                                   |               | ✓         |                                 |                 |           |
| Eligibility screening                         |               | ✓         |                                 |                 |           |
| Informed consent                              |               | ✓         |                                 |                 |           |
| InterFACE-AR orientation/practice             |               | ✓         |                                 |                 |           |
| Randomization                                 |               |           | ✓                               |                 |           |
| INTERVENTION                                  |               |           |                                 |                 |           |
| Intervention group (InterFACE-AR)             |               |           |                                 | ✓               |           |
| Control group (conventional)                  |               |           |                                 | ✓               |           |
| ASSESSMENTS                                   |               |           |                                 |                 |           |
| Demographics + clinical data (CRF)            |               |           | ✓                               |                 |           |
| Primary outcome                               |               |           |                                 |                 |           |
| Time to first dose of epinephrine             |               |           |                                 | ✓               |           |
| Secondary outcomes                            |               |           |                                 |                 |           |
| Time to initiation of CPR                     |               |           |                                 | ✓               |           |
| Time to defibrillation                        |               |           |                                 | ✓               |           |
| Time to delivery of other drugs               |               |           |                                 | ✓               |           |
| Time to definitive airway                     |               |           |                                 | ✓               |           |
| Medication errors (video review)              |               |           |                                 | ✓               |           |
| CPR pauses: frequency/duration (video review) |               |           |                                 | ✓               |           |
| CCF, peri- shock pause via Zoll R Series)     |               |           |                                 | ✓               |           |
| User Experience Questionnaire (UE, survey)    |               |           |                                 |                 | ✓         |
| Technology Acceptance Model (TAM, survey)     |               |           |                                 |                 | ✓         |

**Figure 3.** Standard Protocol Items: Recommendations for Interventional Trials checklist (SPIRIT) figure.

## **6. Data Collection**

### **6.1 Methods of Measurement**

Times to critical interventions (in seconds), including initiation of CPR, time to medication and defibrillation orders, and definitive airway, will be abstracted from a standardized video setup. The scenario will be videotaped from a bird's-eye view angled at 20-30°, using a GoPro Hero 12 Black (San Mateo, CA, USA) mounted on a tripod positioned 7 feet from the foot of the bed and 6 feet 6 inches above the floor, recording in 4K resolution at 60 frames per second (16:9, wide-angle). The camera position and settings will be standardized across sites. Videos will be stored in duplicate on secure, password-protected hard drives in locked rooms at each study site. Adherence to ALS guidelines will be assessed by video review conducted independently by two trained, calibrated raters. Chest compression fraction (CCF) and peri-shock pause duration will be obtained directly from the Zoll R Series defibrillator. Following completion of the scenario, participants will fill out the User Experience Questionnaire, and TAM questionnaire (see secondary outcomes below), all of which have been previously utilized in our previous studies. Compliance with AHA targets will follow published definitions. Study data will be collected and managed in REDCap (Geneva University Hospitals), a secure, web-based platform with audit trails and validated data-capture features, allowing controlled export to statistical software.

### **6.2 Retention and Follow-up**

All activities occur in a single, same-day session. No post-session follow-up is planned. Retention is promoted by scheduling sessions several weeks in advance with managerial approval, issuing confirmation/reminder notices, and on-site check-in to minimize delays. Attendance is logged, and brief rescheduling windows are available on the day if needed.

If a participant discontinues or deviates from the assigned condition, we will record: allocation, reason/timing of discontinuation/deviation, and all outcome data available up to that **point**. These data will be included in the intention-to-treat dataset. No additional outcome collection after the session will occur.

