## 7.2 Group Allocation

Randomization will be conducted in a 1:1 ratio at the level of the team and stratified by study site using an online random number generator. Randomization will be conducted in blocks of two to ensure equal distribution of teams across study arms. Study packages will be prepared with opaque envelopes to achieve allocation concealment. Sequentially numbered recruitment packages provided for each site will contain unique identifier codes for participants, along with study arm assignments. Personnel who enroll participants and those who assign participants to interventions will have no advance access to the sequence. On the trial day, the principal investigators or delegated investigators will obtain written informed consent from participants before any study procedures, and selection criteria will be checked prior to participation in the study. Immediately after written consent, the authorized staff will access only the assignment function to obtain the participant's allocation. Assignment will occur once per participant, with audit trails documenting day and time.

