#### **7.4.6 Secondary outcomes - UEQ and TAM (for intervention group only)**

The User Experience Questionnaire (UEQ) and the Technology Acceptance Model (TAM) survey will be administered to participants in the InterFACE-AR group only. Rather than presenting data for each individual item, we will report the statistical summaries (mean and standard deviation) for each construct within both tools. The UEQ includes six constructs: attractiveness, perspicuity, efficiency, dependability, stimulation, and novelty. The TAM includes two constructs: perceived usefulness and perceived ease of use. For each construct, the mean and standard deviation will be reported, and Cronbach's alpha will be calculated to assess the internal consistency of the items within each construct.

In the case of missing data, a complete case analysis will be conducted. No multiple imputations are planned. All statistical tests will be two-sided with a type one error risk of 5%. All statistical analyses will be performed with R software (version 4.5.0; Foundation for Statistical Computing).

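### One cut-off for stopping and for deviating may cost a team that finishes the scenario its later outcomes, and the primary if the deviation precedes first epinephrine, yet the data are called intention-to-treat

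*Combined protocol and SAP*

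**What the plan says.** Section 6.2 (Retention and Follow-up) sets the rule. Its trigger is an individual and covers two different events: "If a participant discontinues or deviates from the assigned condition, we will record" the allocation, then "reason/timing of discontinuation/deviation, and all outcome data available up to that" point. It continues: "These data will be included in the intention-to-treat dataset". It closes with "No additional outcome collection after the session will occur".

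Four other places bear on it:

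- Section 4 defines the primary outcome as "the interval in seconds from recognition of CA at the start of the scenario to completion of epinephrine injection". This is one time per team.
- Section 7.2 fixes the randomised unit: "Randomization will be conducted in a 1:1 ratio at the level of the team".
- The closing paragraph of section 7.4.6 gives the missing-data rule: "In the case of missing data, a complete case analysis will be conducted. No multiple imputations are planned".
- Section 6.1 takes the times from a video of the scenario, and chest compression fraction and peri-shock pauses from the defibrillator. It does not say that either record ends at a deviation.

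Section 7.4 defines no analysis set. The SPIRIT checklist refers to page 12 for data collected after discontinuation or deviation (item 25b) and to pages 12-16 for who is analysed (item 27b). Within those pages, only section 6.2 mentions intention-to-treat.

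**The concern.** Ending a session and leaving the assigned tool while the team carries on are different events. In the first, nothing more can be observed. In the second, the team still gives the drug, and the video shows when. Section 6.2 applies the same cut-off to both. A cut-off at deviation is an on-treatment rule; an intention-to-treat analysis keeps what happens afterwards.

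The unit is also unclear. The rule is triggered by a participant, while the outcome and the randomised unit are the team of three. The text does not say what one member's deviation does to the team's time.

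The losses would probably be uneven. Section 2.7 foresees failure of the simulator or AR device, and section 8.2 foresees motion sickness with AR and equipment problems. A pocket-card team has no comparable device to take off. Teams lost in this way would come mainly from the InterFACE-AR arm, for reasons connected with the system. If they are slower than the rest, removing them makes the system look better than it was in the teams randomised to it.

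**Working it through.** **1. What the rule reaches.** In section 6.2 the point in question is, grammatically, the discontinuation or deviation. No other section says that outcomes after a deviation are kept. A team whose primary value falls after the cut-off has no value, and the complete-case rule then removes it.

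**2. When the primary is at risk.** Section 7.1 gives a prior median of about 165 s (IQR 139 to 173 s). Section 3.2 gives a scenario of 12 min = 720 s.

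- 165/720 = 23% of the scenario (139/720 = 19%; 173/720 = 24%).
- With the assumed 35 s reduction: (165 − 35)/720 = 130/720 = 18%.

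A deviation in roughly the first fifth of the scenario can therefore cost the primary. A later one leaves it intact and can affect only later outcomes, such as defibrillation, drugs in the later rhythms, and the rest of the compression and pause data.

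**3. The plan's own figures.** SD = (173 − 139)/1.35 = 25.2 s, as stated in 7.1. The 9 teams per arm do not follow from the stated two-sided 5% and 90% power: 2 × [25.2 × (1.960 + 1.282)/35]² = 10.9, so 11 per arm (12 by the noncentral t). That is a separate matter. It is noted here because power at 9 against 9 is 79.0% by the t-test, and because no allowance for lost teams is stated.

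**4. Bias if the mean difference is used.** Suppose k of the 9 intervention teams are each D seconds slower than the mean m of the others. The mean of all nine is m + kD/9. After dropping the k teams it is m, so the benefit is overstated by kD/9. The documents give neither k nor D; both are assumptions.

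| Assumption | k = 1 | k = 2 |
|---|---|---|
| Deviating teams perform like controls (D = 35 s) | 35/9 = 3.9 s (11% of 35 s) | 70/9 = 7.8 s (22%) |
| D = 60 s | 60/9 = 6.7 s (19%) | 120/9 = 13.3 s (38%) |
| D = 0 | 0 | 0 |

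In the first row the intention-to-treat difference is 31.1 s (k = 1) or 27.2 s (k = 2), while the complete-case difference stays at 35 s.

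**5. Bias if the median difference is used.** Section 7.4.2 switches to medians for skewed data. Assume the other teams are normal with SD 25.2 s and the dropped teams are slower than all of them.

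- One dropped: the median of nine is the 5th of eight ordered values, expected 0.1525 SD above the centre. The shift is 0.1525 × 25.2 = 3.8 s, however slow that team is.
- Two dropped: the median of nine is the 5th of seven. The shift is 0.3527 × 25.2 = 8.9 s.

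**6. Precision.** If the 35 s effect holds in the remaining teams, t-test power falls from 79.0% (9 against 9) to 76.2% (9 against 8) or 72.7% (9 against 7).

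**The case against.** The sentence can be read as a promise to keep data: it says that everything available will be recorded and included. It does not say that only earlier data count, that abstraction stops, or that anything is deleted. The last sentence of 6.2 could suggest that collection ends with the session. Sections 2.7 and 8.2 respond to trouble by pausing or stopping, and in a stopped scenario nothing exists beyond that point.

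Part of this stands. A reader might infer that the plan orders observed outcomes to be thrown away; the text does not go that far, and the loss follows only from a literal reading. But the remark about the period after the session does not restore data between the deviation and the end of the scenario. Pausing or stopping does not cover a team that puts the tool aside and carries on.

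Three further inferences are tempting and unsupported:

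- That any abandoned headset costs the team its primary outcome. This happens only if the deviation precedes the completed first injection.
- That one member's deviation censors the whole team, or that ignoring a prompt counts as a deviation. No section says either.
- That the bias is as large as the D/9 formula gives for a very slow team. D = 120 s would give 13.3 s for one team, but that is 4.8 times the design SD (60 s is 2.4 times), has no support in the documents, and would not carry over to a median.

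**Conclusion.** The point holds as a defect of wording with a possible bias. Section 6.2, taken literally and combined with complete-case analysis, may remove a randomised team that finished the scenario, under an intention-to-treat label. For the primary this requires a deviation before first epinephrine; otherwise only later outcomes are exposed.

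The direction favours InterFACE-AR if two conditions hold: deviations fall mainly in that arm, which sections 2.7 and 8.2 make plausible, and deviating teams are slower, which the documents do not show. If they are no slower, the expected cost is precision only. Under the assumptions above, one lost team means about 4 to 7 s on the mean scale, or about 4 s on the median scale, against 35 s. How often this would happen is unknown. The wording should be changed because the correction is simple and the raters, who are not blinded (section 7.3), would otherwise have to interpret the rule case by case.

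**What to change.** Replace the recording sentence in section 6.2 with:

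> If a participant removes or stops using the assigned tool but the scenario continues, all team outcomes are still abstracted from the video and defibrillator to the end of the 12-minute scenario, and the team is analysed in its allocated arm. The time and reason of the deviation are recorded as additional data. Data end early only if the whole scenario is terminated; such teams are reported by arm.

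This separates the two events, settles the unit, and makes the label accurate. A team whose scenario is terminated before epinephrine still falls under the complete-case rule, but the count by arm will be visible.

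The cost is a short change of text; the video and defibrillator already supply the data. The estimate may become somewhat less favourable. If one or two kept teams perform like controls, simulated t-test power is about 65% or 51%, compared with 76% or 73% when they are dropped. The higher figures belong to a comparison restricted to teams that kept using the tool.

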## **7. Statistical considerations**

### **7.1 Power and Sample Size Calculation**

The calculation is based on the primary outcome, time to first epinephrine dose. Prior data report a median of approximately 165 seconds (IQR of 139 to 173 seconds). Using the Greco et al. approach, and using the 1st and 3rd quartiles, we estimate SD as  $(173-139)/1.35 = 25.2$  seconds. With a two-sided

$\alpha=.05$  and 90% power to detect a clinically meaningful absolute reduction of 35 seconds, and assuming similar variability between groups, 18 teams (9 per arm) are required.

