#### 423 **7.4.2 Primary Outcome - Time to administer 1st dose of epinephrine**

424 Due to the small sample size, non-parametric approaches will be used to account for potential violations  
425 of assumptions underlying parametric tests. Boxplots will be generated to assess the distribution of data  
426 in both study arms. If the data are approximately symmetric and normally distributed, the mean  
427 difference will be estimated; if the data are skewed or non-normally distributed, the median difference  
428 will be estimated instead. Bootstrapping with 10,000 resamples will be used to calculate 95% confidence  
429 intervals for the estimated differences. Permutation tests with 10,000 iterations will be conducted to  
430 determine 2-sided p-values.

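### The stated 90% power is wrong: 9 teams per arm with the plan's own SD and effect give about 79%

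*Combined protocol and SAP*

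**What the plan says.** Section 7.1 (Power and Sample Size Calculation) bases the sample size on the primary outcome, time to first epinephrine dose. The source figures are given as "Prior data report a median of approximately 165 seconds (IQR of 139 to 173 seconds". The section converts the quartiles to an SD by dividing their difference by 1.35, which gives 25.2 s. It sets a two-sided alpha of .05 and concludes: "90% power to detect a clinically meaningful absolute reduction of 35 seconds, and assuming similar variability between groups, 18 teams (9 per arm) are required". It names no test or sample size formula, makes no allowance for lost sessions and shows no sensitivity to the SD.

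Three other places bear on the figure:

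- Section 7.2 randomizes teams 1:1, stratified by site.
- Section 7.4.2 plans a two-sided permutation test. The mean difference is used if the data look normal; otherwise the wording is "difference will be estimated; if the data are skewed or non-normally distributed, the median difference".
- The closing paragraph of section 7.4.6 confirms two-sided testing at 5% and complete-case analysis.

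The table template in section 7.4.3 carries 9 teams per arm forward.

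**The concern.** The standardized difference is large (35/25.2 = 1.39), so few teams are needed, but 9 per arm is fewer than a two-sided 5% test requires for 90% power. Section 7.1 is the only justification of the trial's size, and any reader can recompute it from the inputs it gives.

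The stakes are in how the trial is read. A design believed to have a 10% chance of missing a 35-second benefit in fact has about twice that. A non-significant result would then be taken as stronger evidence against a worthwhile effect than it is. That outcome is a real possibility: section 1.2 reports that the team's earlier AR device did not improve epinephrine timing.

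A secondary point is that the SD comes from a conversion that assumes normality, while the quartiles lie 165 − 139 = 26 s below the median and 173 − 165 = 8 s above it. Asymmetry of that kind makes the median branch of the analysis plausible, and that branch has less power.

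**Working it through.** **Inputs, all from section 7.1.** SD = (173 − 139)/1.35 = 34/1.35 = 25.19, rounded to 25.2 s. Difference 35 s. Two-sided alpha .05. Power 90%. Equal SD in both arms. The team is both the unit of randomization and the unit of the primary outcome, so no design effect is needed.

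**Step 1: try to reproduce 9 per arm (normal approximation).**

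n per arm = 2 × (z for alpha + z for power)² × (SD/difference)²

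| Setting | Calculation | n per arm |
|---|---|---|
| Two-sided 5%, 90% power (as stated) | 2 × (1.960 + 1.282)² × (25.2/35)² = 10.89 | 11 |
| Two-sided 5%, 80% power | 2 × (1.960 + 0.842)² × (25.2/35)² = 8.14 | 9 |
| One-sided 5%, 90% power | 2 × (1.645 + 1.282)² × (25.2/35)² = 8.88 | 9 |

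The stated settings give 11, not 9. Nine appears only if the power is set to 80% or the test is made one-sided, and each contradicts section 7.1. The documents do not show which slip, if either, occurred.

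**Step 2: power at 9 per arm.**

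- Noncentrality = 35/(25.2 × √(2/9)) = 2.946.
- t test: df = 16, critical value 2.120, noncentral-t power = **79.0%**.
- Normal approximation: Φ(2.946 − 1.960) = **83.8%**.

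The t-test value is the more accurate at this size, because the normal approximation treats the SD as known.

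**Step 3: teams needed for 90% power (t test).**

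| n per arm | Power |
|---|---|
| 9 | 79.0% |
| 10 | 83.6% |
| 11 | 87.2% |
| 12 | 90.2% |

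So 12 per arm, or 24 teams. The normal approximation gives 11 per arm, or 22 teams.

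**Step 4: what 9 per arm does deliver at 90% power (t test).** A difference of about 41.0 s with SD 25.2 s, or a difference of 35 s with an SD of about 21.5 s.

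**Step 5: the planned test.** Normal data were simulated with means 165 and 130 s, SD 25.2 s and 9 teams per arm, and analysed with a two-sided permutation test. One run of 4,000 datasets with 999 permutations gave 79.2% power for the mean difference and 66.0% for the median difference. Across separate runs the ranges were about 77–80% and 64–68%. The mean version agrees with the t test.

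**Step 6: sensitivity to the SD (t test, 9 per arm, 35 s).** The documents give no alternative SD, so these values are assumptions for illustration: SD 30 s gives 64%, and SD 35 s gives 51%.

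**The case against.** The best defence is that section 7.1 names no test, so 79% is not the only admissible answer: the normal approximation gives 83.8%, with a gap of 2 teams per arm. That is fair as to the range, but it does not rescue the claim. Even the more generous formula is 6 points short of 90%, and the simulated permutation test on means supports the lower figure.

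Site stratification could add precision if the sites differ, but section 7.4.2 has no site term and section 7.1 claims no such gain.

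It can also be said that the error leaves the type I error rate, the estimate and its interval untouched, and that the 95% bootstrap interval planned in section 7.4.2 already limits what a null result can claim. This stands. The interval, rather than design power, should carry the interpretation, so the harm lies in a false design statement and not in a biased analysis.

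Finally, the SD conversion is disclosed and cites a published method, and the SDs of 30 and 35 s have no source in the documents. A sensitivity line is therefore good practice and not the correction of an error. The arithmetic finding does not depend on it.

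**Conclusion.** The concern holds. No two-sided 5% calculation from the stated inputs gives 90% power with 18 teams. Power is 79.0% by the t test (83.8% by the normal approximation), so the chance of missing a true 35-second reduction is about 21% (16% on the generous formula) against the 10% claimed. The shortfall is 4 to 6 teams in total. If the medians are compared, power is roughly two thirds.

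These figures assume normal data, a common SD of 25.2 s and all 18 sessions yielding the primary outcome. A larger SD or lost sessions would lower them. The median figure is a simulation result under normality and is approximate; with truly skewed data it could differ. Why 9 was obtained cannot be settled from the documents.

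**What to change.** Replace the concluding sentence of section 7.1 with wording such as:

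> Eighteen teams (9 per arm) give about 79% power to detect a 35-second reduction in mean time, and 90% power to detect 41 seconds, assuming an SD of 25.2 seconds in each arm and a two-sided alpha of .05 (two-sample t test; simulation of the planned permutation test on means agrees). If medians are compared, power for 35 seconds is about 64–68% under normal data.

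The sentence should name the test, so that the figure cannot be read as covering both branches of section 7.4.2. A line giving power at SDs of 30 and 35 s (64% and 51%) is a useful optional addition. A non-significant result should be interpreted from the confidence interval.

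This costs protocol wording only: no extra teams and no change to design or analysis, but a less favourable stated power.

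The alternative is to keep the 90% claim and enrol 24 teams (t test), which at three participants each is 24 × 3 = 72 participants instead of 54; 22 teams (66 participants) meet it only under the normal approximation. Whether that is feasible depends on recruitment status, which the documents do not show. It would also mean updating the Summary and the table templates in sections 7.4.1 and 7.4.3.
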